### Trial design

2.1

REAL‐ASE (Clinical Trials NCT06144047) is a prospective, non‐randomized, multicentre, interventional study that will be performed across UK neurology centres. A total of 33 adults with epilepsy, treated as part of their routine clinical care across the recruitment sites, will be enrolled.

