5 To investigate the participants' acceptability of real‐world implementation with 24/7 EEG™ SubQ Solution	Raw score for IL01 Post market surveillance: Subject satisfaction form at 2‐months and change over time at 6‐months follow‐up
6 To investigate the participant adherence with 24/7 EEG™ SubQ Solution	Proportion of participants' percentage wear time with 24/7 EEG™ SubQ, across the study period of 6 months
7 To report the performance of 24/7 EEG™ SubQ Solution	Number of Device deficiencies during the study period (6 months)
8 To assess the quality of life with 24/7 EEG™ SubQ Solution	Change over time for average EQ‐5D‐5L scores at baseline, 2 months and 6 months. B Change over time for average Participant Weighted Quality of Life In Epilepsy (QOLIE‐31‐P) scores at baseline, 2‐months and 6 months. C Change over time for average Impact of epilepsy scores at baseline, 2‐months and 6 months. D Change over time for average Perceived Self‐Mastery Over Epilepsy scores at baseline, 2‐months and 6 months
9 To assess the health economic impact of epilepsy for participants that have used the 24/7 EEG™ SubQ Solution	Average Client Services Receipt Inventory (CSRI) scores at 6 months
10 To investigate the cost‐effectiveness of current practice and 24/7 EEG™ SubQ Solution	Quality‐adjusted life‐years (QALYs) score
11 To compare above participant reported outcome measurements (ePROM's) with historical controls obtained in previous study (10.1.4)	Endpoints 8 (A‐D) and 9 (A) compared with the 138 participants in SMILE study in the treatment‐a‐usual arm (xii)31), at baseline and 6 months follow‐up

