### Statistical analysis of secondary outcome measures

4.2

Clinical relevance, changes in the clinical management plan for the participant, degree of confidence level of investigators initiating a change in their participant's clinical management plan, based on the input from the EEG data recorded with 24/7 EEG SubQ Solution, will be assessed by questionnaires.

Participant's reaction to receiving feedback on EEG data recorded with 24/7 EEG SubQ will be captured using an average score on a 10‐point Likert scale (positive (10) to negative (1)).

Adherence, acceptability, and performance will be assessed by: (1) Proportion of total study time (wear time) during which 24/7 EEG SubQ data are collected; (2) Questionnaires; (3) Proportion of Device Deficiencies.

In order to assess quality of life we will assess change over time for average EQ‐5D‐5L scores at baseline, 2 months and 6 months, change over time for average Participant Weighted Quality of Life In Epilepsy (QOLIE‐31‐P) scores at baseline, 2‐months and 6 months, change over time for average Impact of epilepsy scores at baseline, 2‐months and 6 months, and change over time for average Perceived self‐mastery over epilepsy scores at baseline, 2‐months and 6 months.

Costs and health outcomes will be estimated over a lifetime time‐horizon in order to consider longer‐term health and economic implications. Results of analysis will be presented in terms of cost per quality‐adjusted life‐year (QALY) gained. Average Client Services Receipt Inventory (CSRI) scores will be assessed at 6 months.

In order to compare our cohort with similar controls without 24/7 EEG SubQ, we will utilize historical controls from a recently completed study,^32^ which included 198 participants in the Treatment As Usual arm with ≥10 seizures/year. These participants were recruited similarly and completed four outcome measures that we will use at baseline and 6 months and CSRI.

In addition to the above, adverse events will be recorded throughout the study.

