### Statistical analysis methods

4.3

The accuracy of the two groups, i.e., (1) AI‐driven algorithm with rapid expert review applied to 24/7 EEG SubQ data vs. ground truth and (2) self‐reported participant diary vs. ground truth, will be compared in two ways: a correlation‐based comparison and an agreement‐based comparison. For the correlation‐based comparison, we will first estimate Spearman correlation coefficients for both groups to evaluate their monotonic relationship with the ground truth. To compare these relations between the two groups, we will use a Wilcoxon signed‐rank test. For the agreement‐based comparison, we will use the Bland–Altman method to allow us to calculate the mean difference and the limits of agreement to determine if one group consistently over‐r underestimates the ground truth compared to the other group.^33^

Questionnaire‐based data (see Table 1) will be assessed using different methods. For categorical data collected at three different time points (start, 2 months, and 6 months), the Chi‐squared test will be used to assess whether there are significant changes in the distribution of responses over time. Likert scale's and the CSRI will be assessed with descriptive statistics (e.g., mean, median, and frequency distributions) to summarize participant responses. For comparing the quality‐of‐life questionnaires (e.g., EQ‐5D, QOLIE‐31‐P) between the study cohort and historical controls, the Mann–Whitney U test will be used. Differences will be considered significant at *p* < 0.05.

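### Quality of life is compared with non-randomised historical controls by an unadjusted Mann–Whitney U test of an unspecified score, although baseline scores exist in both groups; the timing of CSRI is also contradictory

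*Protocol article*

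**What the plan says.** All of the following is in the protocol article.

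- **Design (section 2.1).** REAL-ASE is a "prospective, non‐randomized, multicentre, interventional study". Its size is given as "A total of 33 adults with epilepsy".
- **Comparator (section 4.2; Table 1, row 11).** Quality of life is compared with the treatment-as-usual arm of an earlier study. On those controls section 4.2 says: "These participants were recruited similarly and completed four outcome measures that we will use at baseline and 6 months and CSRI".
- **Baseline in the trial cohort (section 3.1).** The patient-reported measures are taken at Visit 1, at 2 months and at 6 months.
- **Test (section 4.3).** For the quality-of-life questionnaires, "between the study cohort and historical controls, the Mann–Whitney U test will be used", and "Differences will be considered significant at *p* < 0.05". No covariate, matching or weighting is mentioned. The section does not say whether the test is applied to the 6-month score or to the change from baseline.
- **CSRI.** Table 1 row 9 defines the endpoint as "Average Client Services Receipt Inventory (CSRI) scores at 6 months", and section 4.2 gives the same single time point. Row 11 includes endpoint 9 (A) among the comparisons made at baseline and 6 months. Section 4.3 assigns CSRI to descriptive statistics.

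**The concern.** The two groups were not formed by randomisation. The trial cohort agreed to an implant, routinely keeps a diary, has access to a smartphone and will use an electronic diary (sections 2.3 and 3). Nothing in the article says that the controls met those conditions, so the groups may differ before any device is fitted. A two-sample rank test has no place for a baseline covariate. Whether it takes any account of the starting level depends entirely on which score is put into it, and the plan leaves that open.

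Improved quality of life is one of the aims listed in section 1.2, and the historical arm is the only external comparator for it. A difference declared at p < 0.05 could be a pre-existing difference carried forward, or regression of one. The article names the test, so this is a stated choice and not a detail left to an unseen analysis plan.

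**Working it through.** **Plan's own figure.** The article gives no power or error figure for this comparison. The 85% power in section 2.4 concerns the primary correlation outcome and has no bearing here.

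**Inputs from the article.** Cohort 33. Controls 198 in section 4.2 ("which included 198 participants in the Treatment As Usual arm with ≥10 seizures/year") but 138 in Table 1 row 11 ("compared with the 138 participants in SMILE study"); both were used. Alpha 0.05, taken as two-sided because the article does not say.

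**Assumptions not in the article.** Baseline imbalance b of 0 to 0.5 SD; correlation r between baseline and 6-month score of 0.5 to 0.8; normal scores; no device effect. By 6 months the gap either partly regresses to r × b or persists in full at b.

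**Hand check (138 controls, b = 0.3).** Standard error in SD units: sqrt(1/33 + 1/138) = 0.194 (0.188 with 198).

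- 6-month scores, gap persists: 0.3/0.194 = 1.55; P(|Z + 1.55| > 1.96) = 0.34.
- 6-month scores, gap regresses, r = 0.7: 0.7 × 0.3 = 0.21; 0.21/0.194 = 1.08; probability 0.19.
- Change scores, gap regresses, r = 0.5: shift (1 − 0.5) × 0.3 = 0.15; SD of change sqrt(2 × 0.5) = 1; 0.15/0.194 = 0.77; probability 0.12.
- ANCOVA, gap persists, r = 0.5: unexplained shift 0.15; 0.15/(0.194 × sqrt(1 − 0.25)) = 0.89; probability 0.14.

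**Simulation** (6,000 runs per setting). False-positive rates; ranges run over r = 0.5, 0.7, 0.8 and both control numbers:

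| Baseline imbalance | Gap at 6 months | Mann–Whitney, 6-month score | Mann–Whitney, change | Baseline-adjusted ANCOVA |
|---|---|---|---|---|
| 0 | none | about 5% | about 5% | about 5% |
| 0.2 SD | regresses | 8–13% | 6–8% | 5–6% |
| 0.2 SD | persists | 17–18% | about 5% | 7–9% |
| 0.3 SD | regresses | 12–23% | 8–12% | about 5% |
| 0.3 SD | persists | 32–34% | about 5% | 7–15% |
| 0.5 SD | regresses | 24–55% | 13–26% | 4–6% |
| 0.5 SD | persists | 70–73% | 4–5% | 13–32% |

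The choice between 138 and 198 controls does not change the picture.

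**Precision.** The difference detectable with 80% power is 2.802 × SE × a factor for the score used. With 138 controls and r = 0.7:

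- 6-month scores: 2.802 × 0.194 = 0.54 SD.
- Change scores: 0.543 × sqrt(2 × 0.3) = 0.42 SD.
- ANCOVA: 0.543 × sqrt(1 − 0.49) = 0.39 SD.

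**CSRI.** Row 9 and section 4.2 give 6 months only; row 11 gives baseline and 6 months for the same endpoint. Both cannot describe one data collection.

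**The case against.** The strongest reply is that the plan may already use the baseline. Row 11 refers to endpoints 8 (A–D), which row 8 defines as change over time, so a Mann–Whitney test on change scores is a natural reading. On that reading a stable imbalance does no harm (about 5%). This stands, and it defeats the inference a reader might draw that baseline differences are bound to be reported as device effects. It does not rescue the plan: row 11 also names the two time points without mentioning change, section 4.3 does not settle the matter, and change scores have their own inflation when the gap regresses.

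Four further points stand in part.

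- The size of any imbalance is not in the documents. The controls have at least 10 seizures a year, in line with the trial's own entry criterion, and are described as similarly recruited. That narrows the likely gap without showing that there is none.
- A reader might infer that CSRI has no baseline. The documents do not show this: row 11 names one, and the schedule in Figure 2 is not reproduced in the text available. CSRI is also summarised descriptively, so the criticism of the rank test does not reach it.
- A reader might infer that the cost-per-QALY analysis is left without the mean difference it needs. Section 4.2 describes that analysis separately and does not say that it draws on this test.
- The detailed model could be left to an analysis plan, and Table 1 lists the comparison as a secondary objective. But the article does fix a test, and that test cannot adjust.

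**Conclusion.** The point holds as a risk created by an unadjusted test on an unspecified score. With no device effect and an assumed 0.3 SD imbalance, the false-positive rate on 6-month scores is about 12–23% if the gap partly regresses and 32–34% if it persists. Over 0.2–0.5 SD these become 8–55% and 17–73%. On change scores it is about 5% if the gap persists and 6–26% if it regresses over the same imbalances. All of these rest on the assumed imbalance, r of 0.5–0.8 and normal scores.

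It would be wrong to read ANCOVA as a cure. It holds about 4–6% when the gap regresses as the baseline predicts, but gives 7–15% at 0.3 SD when the gap persists in full. That is well below 32–34% but above nominal, and unmeasured differences remain under any of these methods. The CSRI part is an internal contradiction on timing and no more. The change should be made, but the comparison is secondary in Table 1 and the primary correlation analysis is unaffected.

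**What to change.** 1. In section 4.3, make the comparison with historical controls an ANCOVA of the 6-month score on group and baseline score, adding age, sex and baseline seizure frequency where both data sets hold them. Use robust standard errors and report the adjusted mean difference with its 95% CI.
2. Add a change-score analysis as sensitivity, since the two methods fail under opposite assumptions about the gap. Keep Mann–Whitney as descriptive, and state which score it uses.
3. State that residual confounding remains and that the comparison is exploratory.
4. Reconcile CSRI timing: either state in row 9 and section 4.2 that CSRI is collected at Visit 1, or delete baseline for endpoint 9 in row 11. Correct the control number (138 or 198) at the same time.

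The cost is some rewording and slightly more analysis. If a baseline CSRI is wanted and is not already collected, it is one more questionnaire at an existing visit, and participants already past Visit 1 would lack it.

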## OVERSIGHT AND MONITORING

5

Risk‐based monitoring will be carried out by a clinical study manager at UNEEG medical during the period of the investigation. As most source data in this investigation will be electronically archived, centralized monitoring will be performed continuously by the monitor. However, essential documents such as participant identification list and informed consent will be monitored on‐site.

The first monitoring visit will be an on‐site visit planned after the minimum of three and maximum of five participants have completed their first visit to identify any data entry errors (discrepancy between source data and eCRF), systematic errors caused at the site or by the participant, and provide any necessary help and assistance to the site. Most importantly, the aim will be to identify any issues that have or might have impacted the integrity of data and safety of participants early in the study for corrective actions to be implemented.

Remote monitoring visits will be held with an appointed investigator at each site, to follow up on recruitment, site progress, safety reporting, and on potential queries in the REDCap system or other outstanding issues. Remote monitoring visits will be planned every 4–8 weeks, or per 10 participants enrolled at the site.

The frequency of on‐site monitoring visits will be planned dependently on the outcome of the first on‐site visit, and continuous central monitoring and remote monitoring visits: if major issues are identified, a higher frequency of on‐site monitoring visits might be initiated.

### Harms

5.1

All adverse events or device deficiencies will be reported within REDCap. The coordinating investigator at each site must assess all adverse events that occur on their site. All serious adverse events and serious adverse device effects must be reported to the principal investigator (PI) within 3 calendar days of the site becoming aware of the event. It is the responsibility of the PI to ensure that serious adverse events or serious adverse device effects are reported to national regulatory authorities immediately, but no later than 7 calendar days following the date of awareness by the PI.

If a suspicion of an unacceptable risk to participants develops during the clinical investigation, the PI will suspend the study while the risk is assessed. The PI will terminate the study if an unacceptable risk is confirmed. If monitoring or auditing of the clinical investigation identifies serious or repeated deviations at one of the participating investigation sites, the PI will suspend or terminate the investigation site.

## DISCUSSION

6

Epilepsy is a multifaceted, common neurological disorder with a high burden of morbidity, mortality, and cost.^32^, ^33^, ^34^, ^35^, ^36^, ^37^, ^38^, ^39^, ^40^, ^41^ It is clear that poor seizure control with unexpected seizure occurrence results in a reduced quality of life for people with epilepsy and their families.^42^, ^43^ The development of a robust, accurate approach to seizure detection and recording is therefore of the utmost importance. Given the convenience of mobile devices, wearable technology, and the general desire of people with epilepsy for the integration of these advances into their healthcare,^41^, ^44^, ^45^, ^46^, ^47^ the study described here seems a logical next step. By enhancing the quality of information available to PWE, we may promote improved self‐management resulting in better self‐efficacy, adherence to treatment, and avoidance of seizure triggers.^48^, ^49^ In addition to this, we may also expedite impactful treatment decisions, which ordinarily could take multiple visits to the treating clinician.^50^, ^51^

Our study sets out to address a major issue in epilepsy management by pursuing alternative means of seizure monitoring to enable more reliably informed decision making. A particular strength of this study is the integration of the device into clinical practice without overly stringent inclusion criteria. This allows treating clinicians the freedom to make decisions based on their own interpretation of the solution's capabilities.

There are also some study limitations. Our sample size is small and may not be representative of the whole epilepsy population. Recruitment may prove challenging given the need for implantation and increased demands on the clinician. Clinicians will need to familiarize themselves with reviewing data, which could prove to be time consuming. If the AI‐driven algorithm provided by UNEEG proves to be inadequate from a clinician's perspective, the sheer amount of data analysis may not be feasible for busy clinicians. It also raises issues in the UK, where neurologists are not routinely EEG trained, which necessitates reliance on neurophysiologists, which is potentially quite complicated and labor intensive.

We will determine whether 24/7 EEG SubQ is feasible and acceptable to PWE and clinicians alike. REAL‐ASE hopes to establish new avenues to improve quality of life for PWE.

## ETHICAL APPROVAL

REAL‐ASE was approved by the Bromley Research Ethics Committee in July 2023, reference number 23/LO/0419.

## Data Availability

The data that support the findings of this study are available from the corresponding author upon reasonable request.
